## Abstract

**Background:**

Cricoid pressure is considered to be the gold standard means of preventing aspiration of gastric content during Rapid Sequence Intubation (RSI). Its effectiveness has only been demonstrated in cadaveric studies and case reports. No randomised controlled trials comparing the incidence of gastric aspiration following emergent RSI, with or without cricoid pressure, have been performed. If improperly applied, cricoid pressure increases risk to the patient. The clinical significance of aspiration in the emergency department is unknown. This randomised controlled trial aims to; 1. Compare the application of the 'ideal" amount of force (30 - 40 newtons) to standard, unmeasured cricoid pressure and 2. Determine the incidence of clinically defined aspiration syndromes following RSI using a fibrinogen degradation assay previously described.

**Methods/design:**

212 patients requiring emergency intubation will be randomly allocated to either control (unmeasured cricoid pressure) or intervention groups (30 - 40 newtons cricoid pressure). The primary outcome is the rate of aspiration of gastric contents (determined by pepsin detection in the oropharyngeal/tracheal aspirates or treatment for aspiration pneumonitis up to 28 days post-intubation). Secondary outcomes are; correlation between aspiration and lowest pre-intubation Glasgow Coma Score, the relationship between detection of pepsin in trachea and development of aspiration syndromes, complications associated with intubation and grade of the view on direct largyngoscopy.

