### Study design

This is a prospective randomised blinded controlled study of RSI and CP application within the ED. Due to ethical considerations, a control group without CP applied cannot be included in any study. Instead, this study will exploit the fact that the target range CP of 30 - 40 newtons (N) was applied only 25% of the time by ED staff when tested on a model larynx [29]. The incidence of aspiration (determined by pepsin detection in the trachea) in two groups of patients will be compared; those with conventional CP (and hence about a 25% chance of target range CP), and those with exact sustained target range CP (using weighing scales for direct biofeedback). Longitudinal follow-up of participants will be performed to determine to what degree detection of pepsin in the trachea correlates with the development of clinical aspiration syndromes. In addition the incidence of aspiration as a result of pre-hospital intubation (determined by pepsin detection in the trachea) will be determined.

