### Outcome measures

#### Primary outcome measures

• Rate of aspiration (pepsin detection in tracheal aspirate)

• Treatment for aspiration pneumonitis

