#### Secondary outcome measures

• Grade of laryngeal view

• Detection of pepsin in oropharyngeal aspirates

• Procedural complications associated with intubation

• Immediate complications (associated with RSI) within 30 minutes of intubation

• Lowest pre-intubation GCS

• Survival to 28 days/hospital discharge

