### Sample size

In order to adequately power the trial the variation in the rates of aspiration reported in the literature (0.8% to 22%) must be reconciled. Sellick's original data indicates a rate of 11% [2]. Therefore, assuming a rate of 11% aspiration in the control arm, 0% aspiration in the intervention arm and a power of 90% (alpha error = 0.05), 106 patients must be randomised to each group.

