## Discussion

The primary aim of this study is two-fold. Firstly, by comparing the incidence of aspiration of pepsin in the intervention and control groups and prospectively documenting the benefits and adverse events associated with 30 - 40 N of cricoid force during RSI, it aims to challenge the notion that CP prevents aspiration. Secondly, since the presence of pepsin in the oropharynx will be indicative of aspiration having occurred prior to intubation by virtue of the injury sustained by the patient, determining the incidence of pre-intubation aspiration will allow us to further evaluate the relevance of CP in the RSI algorithm in ED.

The secondary aim of this study is also two-fold. Firstly, defining any observed correlation between aspiration and pre-intubation Glasgow coma score will provide evidence for indications for the use of CP dependent upon the level of patient consciousness. Secondly, a correlation between detection of pepsin in trachea and development of aspiration syndromes will support the use of Fibrinogen plate assay in a clinical setting for their early detection and treatment.

It is conceivable that this research could also give rise to novel therapy. For example, once the incidence of serious aspiration and a pepsin positive assay is identified, the plate assay for pepsin could potentially be performed at the bedside, enabling doctors to treat aspiration pneumonia much earlier. It may also lead to amendments to the algorithm for RSI if CP is found to be deleterious.

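### The primary outcome is defined inconsistently: oropharyngeal pepsin is part of it in the abstract but secondary in the outcome list, and the sample size is tied to neither definition

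*Protocol article*

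**What the plan says.** Four places in the protocol article define or use the main outcome.

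- **Abstract, Methods/design.** A single primary outcome, the rate of aspiration, "determined by pepsin detection in the oropharyngeal/tracheal aspirates or treatment for aspiration pneumonitis up to 28 days post-intubation".
- **Primary outcome measures.** Two bullets: "Rate of aspiration (pepsin detection in tracheal aspirate" (the bracket closes there) and "Treatment for aspiration pneumonitis". The list does not say whether they are components of one outcome or two outcomes. It gives no time window for the second.
- **Secondary outcome measures.** "Detection of pepsin in oropharyngeal aspirates" is listed here.
- **Study design.** "The incidence of aspiration (determined by pepsin detection in the trachea) in two groups of patients will be compared".

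Two further passages bear on the choice. The Discussion states that "the presence of pepsin in the oropharynx will be indicative of aspiration having occurred prior to intubation". The Sample size section works from one pair of rates, "assuming a rate of 11% aspiration in the control arm, 0% aspiration in the intervention arm", with "a power of 90% (alpha error = 0.05" (again the bracket closes there), and does not say which definition of aspiration those rates describe.

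**The concern.** Oropharyngeal pepsin cannot be both part of the primary outcome and a secondary outcome. A patient with pepsin in the oropharynx only is a primary event under the abstract and not under the body.

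This matters because of the meaning that the article gives to the measure. If oropharyngeal pepsin marks aspiration before intubation, the force applied to the cricoid during intubation cannot change it. Counting it adds events at a similar rate to both arms and pulls the comparison towards no difference. One stated aim is to test whether cricoid pressure fails to prevent aspiration, so a diluted contrast favours that very conclusion. The assumed 0% in the intervention arm also becomes untenable as soon as any such event occurs there.

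**Working it through.** **1. Definitions side by side.** Is this patient a primary event?

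| Patient has only | Abstract | Primary outcome list | Study design comparison |
|---|---|---|---|
| Tracheal pepsin | yes | yes | yes |
| Oropharyngeal pepsin | yes | no (secondary) | no |
| Treatment for aspiration pneumonitis | yes | yes, as a component or as its own outcome | no |

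Tracheal pepsin is the only measure that counts in all three columns.

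**2. The plan's own sample size.** Inputs from the Sample size section: p1 = 0.11, p2 = 0, power 90%, alpha 0.05 (sidedness not stated; two-sided taken). The mean rate is p̄ = 0.055.

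n0 = [1.960·√(2·p̄·(1−p̄)) + 1.2816·√(p1(1−p1) + p2(1−p2))]² / (p1−p2)²

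= [1.960 × 0.3224 + 1.2816 × 0.3129]² / 0.0121 = 1.0329² / 0.0121 = 88.2, so 89 per arm.

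With continuity correction: n = (n0/4)·[1 + √(1 + 4/(n0·0.11))]² = 22.04 × [1 + √1.4124]² = 105.6, so **106 per arm**. The stated figure is reproduced. The arithmetic is sound, but it covers one binary outcome with no events in the intervention arm.

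**3. Effect of adding unaffected events.** Assumption: the composite adds b percentage points of events to both arms, equally, and cricoid pressure does not alter them. The documents give no value for b, so a range is shown. Power is the sum, over all pairs of event counts at 106 per arm, of the binomial probabilities of those pairs for which the two-sided Fisher p-value is at most 0.05.

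| b (assumed) | Control v intervention | Exact Fisher power |
|---|---|---|
| 0 | 11% v 0% | 98.0% |
| 1 | 12% v 1% | 91.5% |
| 2 | 13% v 2% | 85.4% |
| 5 | 16% v 5% | 69.5% |
| 10 | 21% v 10% | 53.4% |

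A second model gives the same picture. Let background events occur independently of the others, so that the control rate is 1 − 0.89·(1−b) and the intervention rate is b. For b = 2%, 5% and 10%, the uncorrected normal formula gives power of 85.6%, 71.2% and 52.5%. The size needed for 90% power, with continuity correction, is 140, 194 and 291 per arm.

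**4. Error rate if there were two separate primaries.** Two independent tests at a true 0.05 each give 1 − 0.95² = 9.75%. Fisher's test is conservative here: its actual size at 106 per arm is 2.2% at a common rate of 5% and 3.0% at 11%. Two independent Fisher tests would then give 1 − 0.978² = 4.4% to 1 − 0.970² = 5.9%.

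**The case against.** The strongest reply is that the body of the article leans to tracheal pepsin: it is the measure in Study design and the first primary bullet. The clearest outlier is a condensed abstract. That is fair. A reader might infer that the trial has no identifiable primary result, and the text does not support going that far. The contradiction over oropharyngeal pepsin remains, because both statements are current and an unseen analysis plan would have to depart from one of them.

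A reader might also infer two primary outcomes, each tested at 0.05, with an inflated error rate. No section says so. The abstract joins the same items with an "or", so the two bullets may be components of one outcome, and a rule for sharing alpha is commonly left to a fuller plan. The 9.75% is conditional. It also assumes independence and exact 5% tests, whereas aspiration and its treatment are plausibly correlated. Likewise, a reader might infer that the definition could be chosen after the data are seen; an unseen plan may already fix it.

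A third tempting reading treats late pneumonitis as unaffected by cricoid pressure. Nothing in the article says this, and pneumonitis treated within 28 days could follow aspiration at intubation. Only oropharyngeal pepsin is labelled as preceding intubation.

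Finally, tracheal pepsin is not free of earlier events. The Background notes that an earlier study using the assay could not separate aspiration before intubation from aspiration at intubation. Choosing tracheal pepsin removes the component that the article itself assigns to the earlier period; it does not remove every such event.

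**Conclusion.** The point stands as an internal inconsistency in the definition of the primary outcome. Oropharyngeal pepsin is primary in one place and secondary in another. The role of treatment for pneumonitis is unclear, and the 11% against 0% belongs to no named definition. None of this depends on a calculation.

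The size of the dilution does depend on an assumption. With 1 point of unaffected events, power is still above the planned 90%. At 2 points it is below, and at 5 to 10 points it falls to 70% to 53%. These figures assume an equal background in both arms and an unchanged 11-point difference. Inflation of the familywise error is not established; it would arise only if the two bullets were tested separately at 0.05 each, and then to at most about 9.75% under independence.

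**What to change.** State one primary outcome in the same words in the abstract, Study design, Primary outcome measures and Sample size, and remove oropharyngeal pepsin from the primary definition. Tracheal pepsin (yes/no), compared at two-sided 0.05, is the natural choice, because it is the only measure common to the abstract's definition, the Study design comparison and the primary list. Tie the 11% against 0% assumption to it; the stated inputs then still give 106 per arm.

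Treatment for aspiration pneumonitis to 28 days would become secondary, with its window written into the list. This changes the current primary list. If the sponsor prefers to keep it primary, say whether it is a component of a composite or a co-primary, match the sample size assumption to that choice and, if it is tested separately, state how alpha is handled.

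The cost is wording. The aspirates and the 28-day review of notes are already planned, so no data collection changes. The downside is that one outcome may lose the label of primary. The article gives the trial status as ongoing, so the change should be made before any comparison of the arms is seen.

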**Discussion:**

The benefits and risks of cricoid pressure application will be scrutinised by comparison of the incidence of aspiration and difficult or failed intubations in each group. The role of cricoid pressure in RSI in the emergency department and the use of a pepsin detection as a predictor of clinical aspiration will be evaluated.

**Trial registration:**

Australian New Zealand Clinical Trials Registry (ANZCTR): ACTRN12611000587909

## Background

Rapid sequence intubation (RSI) is the process by which anaesthetic and neuromuscular blocking agents are administered in rapid succession to facilitate endotracheal intubation [1]. In the emergency department (ED) RSI is typically performed on acutely ill or injured patients who are often not fasted, increasing the risk of gastric aspiration during the process. In 1961 Sellick reported using "occlusion of the upper oesophagus by backwards pressure on the cricoid ring against the bodies of the cervical vertebrae to prevent gastric contents from reaching the pharynx" during induction of anaesthesia in patients at high risk of aspiration [2]. Cricoid pressure (CP) was subsequently adopted as an integral component of RSI in EDs despite inadequate scientific evaluation of its risks and benefits; its effectiveness has subsequently only been demonstrated in cadavers [3-6]. No randomised controlled trials have shown any benefit of its use during RSI. Furthermore the application of CP may be associated with increased risks to the patient: impeding airway management [7,8]; prolonging intubation time by obscuring laryngeal view [9,10]; inducing nausea/vomiting [10] and oesophageal rupture with excessive force [11]. Paradoxically, CP may indeed promote aspiration by relaxing the lower part of the oesophagus [12]. Some case reports note that tracheal intubation was impeded by CP [13] and regurgitation occurred despite application of CP [14,15], possibly due to its improper application.

Ostensibly a simple procedure, CP is in practice a complex manoeuvre which is difficult to perform optimally [12]. The amount of force used by the cricoid operator is a crucial factor in proper application of CP. A force in the range of 30 - 40 Newtons (N) applied to the cricoid ring is generally accepted as sufficient to occlude the oesophagus [5,12,16-18], preventing regurgitation of gastric contents. Studies have revealed that the knowledge of cricoid force theory and concept of the forces required is poor amongst both anaesthetic and ED staff [19-31]. Considerable ranges in the amount of force used by staff when applying force to cricoid models have been described [29,31,32]. Furthermore, when ED staff were asked to apply "ideal" CP to a human larynx model, only 25% of the group reached the target range, while 47% applied insufficient and 28% applied excessive force [29]. At forces greater than 44 N the patient is considered to be at risk of oesophageal rupture [5,10]. Training staff how to gauge the correct amount of force to use is effective in the short term only, however, in practice training is rarely undertaken [23,25,26,31,33,34]. In addition, the effect of fatigue on the ability of the cricoid operator to maintain CP within the target range for the duration of prolonged intubations has been questioned [35]. The use of floor scales to provide a means of gauging the amount of force applied to a cricoid model has been demonstrated [25], however its use in real-time measurement during RSI has not been reported.

Aspiration of gastric or oropharyngeal contents into the larynx and lower respiratory tract may lead to various pulmonary syndromes, most notably pneumonia and pneumonitis. The true incidence and clinical significance of aspiration during RSI is difficult to establish due to the heterogeneous nature of pathologic processes of critically ill patients requiring an emergency airway. Compounding this is the fact that many patients aspirate prior to intubation or arrival at ED and that repeated attempts at intubation increased the incidence of aspiration (Mort et al. 2004). Mort reported that the rate of aspiration increased from 1.9% with one attempt at intubation to 22% with three or more attempts [36]. Given these limitations, the incidence of aspiration appears to lie anywhere between 0.8% [36] and 22% [37]. There is currently no widely available test to determine whether pulmonary aspiration has occurred during RSI. Pepsin detection has been described as a potential aspiration biomarker [38] since it is uniquely secreted in stomach. Ufberg has developed and validated a specific and sensitive pepsin assay as a marker of aspiration [39]. Using the assay he found pepsin in the lungs in 50% of patients intubated in the pre-hospital setting, and 22% of patients undergoing RSI in the ED [37], however there was no longitudinal follow-up to see whether the presence of pepsin in the lungs was linked to subsequent development of aspiration syndromes. It was also not possible to determine if aspiration occurred prior to or at the time of intubation.

The value of CP in RSI is under increasing scrutiny [40,41]. Since its introduction in the 1960s anaesthesia practices and airway management techniques have improved leading some to wonder what contribution CP now makes towards reduced aspiration rates [40]. Critically ill patients presenting to the ED are also likely to have aspirated prior to intubation [40], therefore negating necessity for CP in the ED.

Emergency physicians today need evidence to support the use of CP in the ED. The current study aims to address these issues, being designed to evaluate the effectiveness, safety and need for CP during RSI in EDs.

### Study design

This is a prospective randomised blinded controlled study of RSI and CP application within the ED. Due to ethical considerations, a control group without CP applied cannot be included in any study. Instead, this study will exploit the fact that the target range CP of 30 - 40 newtons (N) was applied only 25% of the time by ED staff when tested on a model larynx [29]. The incidence of aspiration (determined by pepsin detection in the trachea) in two groups of patients will be compared; those with conventional CP (and hence about a 25% chance of target range CP), and those with exact sustained target range CP (using weighing scales for direct biofeedback). Longitudinal follow-up of participants will be performed to determine to what degree detection of pepsin in the trachea correlates with the development of clinical aspiration syndromes. In addition the incidence of aspiration as a result of pre-hospital intubation (determined by pepsin detection in the trachea) will be determined.

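### The Study design section carries over only the 25% of operators in range and omits the 28% above it; the aspiration contrast may be nearer 47 than 75 points, and the 90% power depends on what the undefined 11% means

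*Protocol article*

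**What the plan says.** The Study design section says that a control group without CP is ruled out on ethical grounds. In its place the trial will use the low rate at which emergency staff hit 30-40 N on a model larynx. The two groups are "those with conventional CP (and hence about a 25% chance of target range CP), and those with exact sustained target range CP".

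The Background cites the same source and gives the whole distribution: "only 25% of the group reached the target range, while 47% applied insufficient and 28% applied excessive force [29". It describes 30-40 N as "generally accepted as sufficient to occlude the oesophagus". The harm it attaches to high force, above 44 N, is oesophageal rupture.

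Under Control arm, the operator also aims for 30-40 N, with the scale display covered.

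The Sample size section takes 11% from the original case series of the technique. It then sets the calculation as "assuming a rate of 11% aspiration in the control arm, 0% aspiration in the intervention arm and a power of 90% (alpha error = 0.05"), from which "106 patients must be randomised to each group". None of the force percentages appears there, and the section does not say whether the 11% was observed with or without CP.

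The first primary aim under Study objectives is to test the hypothesis that CP in emergency intubation does not prevent aspiration.

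**The concern.** The primary outcome is aspiration. By the Background's own mechanism, what matters for it is whether the force is enough to close the oesophagus. The share of controls inside a two-sided target range answers a different question, because an operator who presses too hard misses the range without necessarily losing occlusion. Quoting only the 25% makes the control arm look further from the intervention arm than the full distribution suggests.

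Two things are at stake. The first is power: if the 11% is a rate without adequate CP, it should have been reduced for the controls who do receive adequate force. The second is interpretation. The stated hypothesis is that CP does not prevent aspiration, so a null result favours the investigators' thesis. If about half the controls receive occluding force, a null result becomes more likely even when CP works, and it could be over-read.

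**Working it through.** **Inputs from the documents.** Force split 25% / 47% / 28% (Background). Rates 11% and 0%, power 90%, alpha 0.05, 106 per arm (Sample size). Whether the test is one- or two-sided is not stated; two-sided is assumed because it reproduces the plan's figure.

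**Step 1: reproduce 106.** With p = 0.11 v 0 the mean rate is 0.055, and

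n0 = [1.960 × √(2 × 0.055 × 0.945) + 1.282 × √(0.11 × 0.89)]² / 0.11² = 88.2.

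The continuity correction gives n = (n0/4) × [1 + √(1 + 4/(n0 × 0.11))]² = 105.6, rounded up to 106. This is an exact match. Without the correction the answer is 89.

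**Step 2: the contrast in force.** Take the intervention arm as 100% in range, as the design intends.

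- If only in-range force protects: 100 − 25 = 75 percentage points.
- If force above the range also occludes: 25 + 28 = 53% of controls are protected, and 100 − 53 = 47 percentage points.

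**Step 3: the control rate under each meaning of the 11%.**

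- Average under conventional CP: the control rate is 11% as entered, and nothing needs diluting.
- Rate without adequate CP, with adequate force giving 0% (the intervention-arm value in the Sample size section): 0.75 × 11% = 8.25% if only in-range force protects, or 0.47 × 11% = 5.17% if excess force also protects.

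**Step 4: power at 106 per arm v 0%.** The Step 1 formula is inverted by using an effective size m = 106 × [1 − 1/(106p)]². Fisher's exact test is shown beside it because the Analysis section allows it and expected counts are small. With no events in the intervention arm, it needs at least 6 control events for p ≤ 0.05 (5 events give p = 0.060, 6 give p = 0.029).

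| Control rate | Expected control events | Corrected formula | Fisher exact | Per arm for 90% (corrected formula) |
|---|---|---|---|---|
| 11% | 11.7 | 90% | 98% | 106 |
| 8.25% | 8.7 | 77% | 88% | 144 |
| 5.17% | 5.5 | 49% | 47% | 233 |

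**Step 5: if excess force itself raises aspiration.** These two rates in over-forced controls are assumptions for illustration only, with 11% kept in under-forced controls.

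- 15%: 0.47 × 11% + 0.28 × 15% = 9.4%; power 83% (Fisher 94%).
- 22%: 0.47 × 11% + 0.28 × 22% = 11.3%; power 91% (Fisher 98%).

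**The case against.** The strongest reply is that the Sample size section assigns 11% to the control arm itself. The control arm is conventional CP, so on its face 11% is already the average over light, correct and heavy force, and 106 per arm needs no adjustment. This stands as one of two readings. It does not settle the matter, because the 11% is drawn from an early case series and the protocol does not say which kind of rate that was.

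Three further replies have force.

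- That force above 40 N prevents aspiration is inferred from the Background, not stated there. The Background also says that CP may impede airway management, induce vomiting and even promote aspiration.
- The split was measured on a larynx model, and reaching 30 N on a model is not sustained occlusion in a patient. The same limit applies to the 25% that the design relies on.
- By Fisher's exact test, power at 8.25% is 88%, close to the stated 90%. Only the 5.2% case is seriously short.

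Two stronger arguments may tempt a reader and should not be used.

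- One is that an 11% control average would imply 11/0.47 = 23.4% in under-forced controls, which is above the 22% at the top of the quoted literature range. That sets a subgroup rate against overall rates. The Background also reports pepsin in 50% of patients intubated before hospital, so 22% is not a ceiling.
- The other is that power must lie between 49% and 77%. Step 5 shows that it can be higher if excess force raises aspiration.

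**Conclusion.** The concern holds in a conditional form. The Study design section leaves out the 28% above range. On the Background's own labels, only 47% of operators applied too little force. The contrast for aspiration is therefore better stated as 47 to 75 percentage points. The lower end assumes that force above the range occludes, and both ends assume that the model data carry over to patients.

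The effect on power depends on an undefined input. If 11% is the conventional-CP average, the stated 90% at 106 per arm stands. If it is the rate without adequate CP and adequate force gives 0%, power is about 77% or 49% by the plan's apparent formula (88% or 47% by Fisher's exact test).

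A reader might infer that the trial lacks its stated power outright, or that the protocol treats every off-target control as unprotected. The documents support neither: the first depends on the unstated meaning of the 11%, and the second is nowhere said.

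The limit on interpretation does not depend on the 11%. Both arms receive CP, so a null result compares measured with unmeasured CP. It does not show that CP fails to prevent aspiration.

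**What to change.** - **Study design:** give the full 25 / 47 / 28 split, state the expected contrast for aspiration as 47 to 75 percentage points, and note that it comes from a larynx model.
- **Sample size:** say whether 11% is the average under conventional CP or the rate without adequate CP. Replace the unqualified 90% with power at 106 per arm across control rates of about 5% to 11%, and name the method (continuity-corrected formula or Fisher's exact test).
- **Study objectives and Discussion:** state that a null result compares measured with unmeasured CP and is not evidence that CP does not prevent aspiration. The scale recordings, logged at 60 points per second with operators in both arms standing on the scales, can show how far the arms actually differed in force. They help guard against over-reading a null result but do not restore power.

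The cost is rewording only, with no extra patients or data. The downside is a stated power that looks less favourable over part of the range.
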